### Participants and setting

An overview of the recruitment and participant timeline can be found in Fig. 2. In this RCT, dyads will participate each consisting of a person living with dementia, who attends a day-care centre and his or her informal caregiver. Participants with dementia can be either existing or new visitors of a day-care centre in the Netherlands.

**Fig. 2 Fig2:**
[figure not shown]
Flow chart of the recruitment and participant timeline

### Inclusion criteria

Inclusion criteria are as follows. The participant with dementia has to live in the community and not foreseen to be admitted in a care home in the coming six months. He or she has to visit the day-care centre for at least two days per week. If the participant is admitted to a nursing or care home, stops visiting the day-care centre during the six months of data collection, and/or deceases his/her participation in the trial will be withdrawn. There has to be a diagnosis of mild to moderate dementia (MMSE score between 10 and 24), without any restriction to the type of dementia (i.e. Alzheimer’s Disease, frontotemporal dementia, vascular dementia), or the authority, who has given the diagnosis (i.e. general practitioner, neurologist, memory clinic). There has to be an informal caregiver present, who is willing to participate in interviews and to keep track of the healthcare costs of themselves and the participant with dementia.

### Exclusion criteria

Exclusion criteria are as follows. Severe physical disorders or diseases, which would make it impossible for the participant with dementia to take part in an exergaming activity. Terminal diseases (other than dementia).

### Recruitment

Participants are recruited by the staff of the day-care centres. Each day-care centre has a local project coordinator (i.e. physiotherapist, activity coordinator) assigned among their staff. This person is instructed by the research team on how to recruit participants and supervise the intervention and data collection.

To inform potential participants the project coordinator at the day-care centres offers an information package to the person with dementia and their informal caregiver.

Informal caregivers are offered a small compensation (worth € 25,-) for their participation in the research project. The compensation is meant as an extra motivation for them to take part, especially because informal caregivers can often feel burdened which might refrain them from participating [49]. It is not compulsory to finish the entire data collection trajectory (i.e. all interviews and tests for both informal caregiver and participant with dementia) in order to receive the compensation.

### Sample size calculation

Since a high quality study evaluating the effect of a similar intervention on physical activity and mobility was not available when we were writing our protocol, we used previous results on exergaming regarding one of our secondary outcome measures (memory) for this power calculation [38]. We performed a power analysis based on a power of 80% and a difference of 2 (with a standard deviation of 4.6) between scores on the Mini-Mental State Examination (MMSE) [50]. We chose an Intracluster Correlation Coefficient (ICC) of 0.05. This resulted in a sample size of 166 participating dyads with an alpha of 0.05. When also taking into account the cluster effect of the day-care centres (7 dyads per cluster) and drop out (4%), the total sample size needed is 224 dyads.

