## Methods

### Study design and setting

We will study the effectiveness and cost-effectiveness of exergaming in a cluster RCT using a randomized controlled block design. All aspects of this trial (design, conduct, and reporting) will adhere to the requirements of the SPIRIT statement (Standard Protocol Items: Recommendations for Interventional Trials) [45, 46] as well as to the Consolidation Standards of Reporting Trials (CONSORT) guidelines [47]. A completed SPIRIT checklist of our trial protocol is available upon request. We will compare people with dementia (and their informal caregivers), who visit day-care centres which offer exergaming to people with dementia (and their informal caregivers), who visit day-care centres that offer regular activities regarding the following outcome variables: physical activity, mobility and physical, cognitive, emotional and social functioning, quality of life of people with dementia and their informal caregivers, experienced burden and positive care experiences of the informal caregivers, and societal costs. The comparator of regular activities at day-care centres without exergaming has been chosen, to ensure that any between-group effect we will find, can be contributed to the exergaming intervention.

Interviews and tests will be scheduled at the start of the study (baseline), after three and after 6 months (two follow up measurements). In total, 24 day-care centres will be recruited. All day-care centres are located in the Netherlands, there are no restrictions to which parts of the country. A list of the study sites will be available upon request. The process analysis will only be carried out in the experimental group.

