**Fig. 1 Fig1:**
[figure not shown]
Flow chart of the randomization of day-care centres

We will (if possible) arrange blocks of centres that are similar to one another (in terms of region and/or target group: i.e. severity of dementia, age of onset, ethnicity, group size in the day-care centre). This is to control for environmental factors that might possibly influence the outcomes. Within these blocks, day-care centres will be randomized by an independent researcher, using Random Allocation Software [48], to either the experimental (exergaming) group or control (regular activities) group (12 day-care centres per group). After randomization, the day-care centres will remain in the experimental or control group throughout the duration of the trial.

Day-care centres which already have the required exergaming equipment, will be paired up with a comparable day-care centre from the same or another care organization without the equipment. Then they will be randomized as a pair instead of as an individual day-care centre. If this pair is randomized in the experimental group, the day-care centre with the exergaming equipment will participate in the trial. Similarly, if this pair is randomized in the control group, the day-care centre without the equipment will participate in the trial. Day-care centres which do not have any exergaming equipment yet, can also be enrolled for randomization individually if they are willing and able to buy the exergaming equipment needed for the trial. This has to be confirmed, prior to randomization, and is intended to ensure they can still participate when they are randomized to the experimental group.

Day-care centres in both groups will each receive an allowance of at most € 1.125,-. When they recruit eight persons or more. They can decide themselves how they want to spend this, for example to pay their staff for the extra hours they have to put in to participate in the research project. Day-care centres in the experimental group may also put this amount towards the purchase of the exergaming equipment.

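### The 224-dyad sample size assumes 7 dyads per centre, but 24 centres means 9.33 per centre, so power for MMSE is about 77%, not 80%

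*Protocol article*

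**What the plan says.** All the inputs are in the protocol article. The Sample size calculation section specifies 80% power for "a difference of 2 (with a standard deviation of 4.6) between scores on the Mini-Mental State Examination (MMSE"), and adds: "We chose an Intracluster Correlation Coefficient (ICC) of 0.05". It then gives the size before clustering: "This resulted in a sample size of 166 participating dyads with an alpha of 0.05". The last step allows for the "cluster effect of the day-care centres (7 dyads per cluster) and drop out (4%), the total sample size needed is 224 dyads".

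The same section is open about the endpoint. No suitable study on physical activity or mobility was available, so "we used previous results on exergaming regarding one of our secondary outcome measures (memory) for this power calculation".

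The number of centres is fixed elsewhere. Study design and setting states: "In total, 24 day-care centres will be recruited". The Methods paragraph of the abstract gives 24 centres together with 224 dyads, and the section on recruitment and randomization of day-care centres gives 12 centres per group. The only other per-centre number is in that last section, where the centre allowance is tied to recruitment: "When they recruit eight persons or more".

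**The concern.** Seven dyads per cluster, 24 centres and 224 dyads cannot all be true: 24 × 7 = 168, and 224 / 7 = 32. The article nowhere mentions 32 centres or an average above 9 dyads per centre. The cluster size matters because it sets the design effect. With the number of centres fixed, adding dyads to each centre raises the variance inflation, so each added dyad brings less information than the calculation assumes.

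At stake is the stated 80%. It belongs to a 32-centre trial, and readers of the results would judge an inconclusive MMSE comparison against a power figure slightly higher than the 24-centre design provides.

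**Working it through.** **Inputs (Sample size calculation):** difference 2, SD 4.6, power 80%, alpha 0.05, ICC 0.05, 7 dyads per cluster, drop-out 4%, total 224. **Inputs (elsewhere in the article):** 24 centres, 12 per group. The sidedness of alpha is not stated. A two-sided test reproduces the 166; a one-sided test would give 132.

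**Step 1: reproduce the plan's figure.**
- Per arm: 2 × (1.960 + 0.842)² × (4.6/2)² = 83.04, so 166 in total. This agrees.
- Design effect at 7 per cluster: 1 + (7 − 1) × 0.05 = 1.30.
- 166 × 1.30 = 215.8.
- Drop-out: 215.8 / 0.96 = 224.8, or 215.8 × 1.04 = 224.4. Either matches 224 up to rounding.

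So 224 comes from the 1.30 design effect.

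**Step 2: the design that 224 belongs to.** 224 / 7 = 32 centres. After 4% drop-out, 215.04 dyads are analysed, or 6.72 per centre. The design effect is 1.286, the effective N is 167.2 and power is 80.3%. Keeping 7 in the design effect gives 79.8%. For 32 centres the 80% claim is correct.

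**Step 3: the design the article describes.** Effective N = analysed N / [1 + (m − 1) × 0.05]. The standard error of the difference is 4.6 × √(4 / effective N). Power is Φ(2/SE − 1.960), ignoring the negligible opposite tail.

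| 24 centres, ICC 0.05 | Analysed | m | Design effect | Effective N | Power |
|---|---|---|---|---|---|
| 224 dyads, 4% drop-out | 215.04 | 8.96 | 1.398 | 153.8 | 76.9% |
| Same, design effect from recruited size | 215.04 | 9.33 | 1.417 | 151.8 | 76.4% |
| 224 dyads, no drop-out | 224 | 9.33 | 1.417 | 158.1 | 78.0% |
| 168 dyads (7 each), 4% drop-out | 161.28 | 6.72 | 1.286 | 125.4 | 68.2% |

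First row written out: SE = 4.6 × √(4/153.8) = 0.742; 2/0.742 = 2.70; Φ(2.70 − 1.96) = 0.77.

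**Step 4: detectable difference with 80% power, first row.** (1.960 + 0.842) × 0.742 = 2.08 MMSE points, or 2.08/4.6 = 0.45 SD. The plan is 2.00 points, or 2/4.6 = 0.435 SD.

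**Step 5: sensitivity.**
- ICC, for 224 dyads in 24 centres with 4% drop-out (values other than 0.05 are assumptions): 84% power at 0.02, 82% at 0.03, 79% at 0.04, 77% at 0.05, 66% at 0.10.
- Reference distribution: a noncentral t with 24 − 2 = 22 degrees of freedom gives 73.1% for the first row and 64.3% for the last. The article specifies no such test, so this is a sensitivity figure only.

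**The case against.** The strongest reply is that the effect is small. The abstract states both 24 centres and 224 dyads, so the natural reading is that 224 would be enrolled. On that reading the loss is about 3 percentage points, or 0.08 of an MMSE point in the detectable difference. The ICC of 0.05 was simply chosen, and moving it to 0.03 puts power back above 80%. This stands as an argument about size. It does not rescue the calculation, which states 0.05 and is inconsistent at that value. It would give less than 80% in 24 centres even if nobody dropped out.

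A reader might infer several stronger things that the article does not support:

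- **That the trial has only 68% power.** This needs centres to stop at 7 dyads each and abandons the 224 given in two places.
- **That 192 dyads were expected, from 24 × 8.** Eight persons is a condition for paying the allowance; it is neither a cap nor a planned average.
- **That the true figure is 73%, from a t distribution on 22 degrees of freedom.** The article plans a mixed model with blocked allocation and names no degrees-of-freedom method, a detail that may sit in a fuller document. The issue is also separate: 32 centres of 7 would fall to 77.6% on the same kind of calculation with 30 degrees of freedom.
- **That basing power on MMSE is a hidden error.** The article says openly that MMSE is a secondary outcome and why it was used. It does not present 80% as the power for physical activity or for the Short Physical Performance Battery (SPPB).
- **That 4% drop-out is contradicted.** The inclusion criteria list reasons for withdrawal but give no rates, and those who drop out are to be kept in the main analysis by multiple imputation. One may doubt 4%, but no figure in the article refutes it.
- **That 0.45 SD is the detectable difference for the primary outcomes.** The article gives no ICC for SPPB or physical activity, so this would carry the ICC of the MMSE calculation over to other endpoints.

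**Conclusion.** The point holds as an internal inconsistency with a modest consequence. The stated total rests on a cluster size that the 24-centre design cannot have at 224 dyads. With 24 centres and 224 dyads, power for the planned MMSE difference is about 77% rather than 80%. It would be about 68% only if centres recruited 7 each.

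These figures assume the article's ICC of 0.05 and 4% drop-out, a two-sided 0.05 test, the normal approximation and equal cluster sizes. Unequal centres would lower power further. Baseline adjustment or repeated measures might raise it, but the stated calculation counts on neither. The planned estimates, tests and confidence intervals are unaffected. The paragraph should be corrected, but the error does not undermine the trial.

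**What to change.** Rewrite the last part of the Sample size calculation section so that cluster size, number of centres and total agree. For example: with 24 centres and 224 recruited dyads (9.33 per centre; 8.96 after 4% drop-out), an ICC of 0.05 and a design effect of about 1.40, power to detect an MMSE difference of 2 (SD 4.6) at two-sided alpha 0.05 is about 77%, and the difference detectable with 80% power is about 2.08 points. If 7 per centre was the real expectation, say so and give 168 dyads with about 68%.

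The t-based 73% may be added as a labelled sensitivity figure. Give no detectable difference for SPPB or physical activity unless the ICC used for them is labelled as an assumption and shown over a range.

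The Trial status section reports that inclusion ended in September 2018, so the trial should not be enlarged. The cost is one reworded paragraph and a slightly less favourable power figure.

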### Intervention and materials

Participants with dementia visiting a day-care centre assigned to the experimental group will be asked to take part in the exergaming intervention, which consists of interactive cycling. This type of exergaming has been selected for this research study, because is it a recognizable physical activity, especially in the Netherlands where cycling is very common. During interactive cycling, the participant cycles on a stationary bicycle (i.e. Thera trainer or home trainer) that is connected to a digital screen. The participant can cycle a route and is thus physically and cognitively stimulated. It is also possible to place multiple bicycles in one room. The exergames vary in physical and cognitive challenges and level of interaction. Interactive cycling on a stationary bicycle is made possible by specific software and sensors: the participant’s cycling speed regulates the images on a digital screen. Motion sensors are attached to the pedals of the bicycle. Depending on the chosen software, specific interactions are possible, such as making left or right turns on junctions, or creating an own route using *Google Street View*©. The available routes vary per program, examples of routes are Amsterdam city centre, Rotterdam Blijdorp Zoo, the Betuwe (area in the Netherlands with lots of orchards), Rome, and Tokyo.

Day-care centres participating in the study already have the exergaming equipment or can buy or lease it from various providers. The companies Embedded Fitness and SilverFit participate in the research project as partners. Within the context of this research project, they offer participating day-care centres four different kinds of exergaming systems with a discount: “*Fietslabyrint*©”, “*SilverFit Mile*©”, “*PraxFit*©” or “*DiFiets*©”. The software, sensors and the digital screen can be connected to any kind of exercise equipment with a pedalling mechanism. This means that if a day-care centre already has a stationary bicycle, they do not need to purchase a new one. If this is not the case, SilverFit and Embedded Fitness sell a wide selection of stationary bicycles.

Because purchasing exergaming equipment can be costly, day-care centres in the experimental group each receive an extra allowance of € 1.500,-. The research team also provides them with a list of organizations where they can apply for additional funding.

The research team supports the day-care centres in choosing the exergaming equipment best suited to their needs in terms of type of stationary bicycle which fits the target group as well as the available facilities at the location. This is done based on the results of previous research carried out by the Coalition of Applied Gaming [35], the expertise of the research team and interviews with (representatives of) people with dementia from participating day-care centres. The research team will also advise with regard to the space where and manner in which the exergaming activity will be offered (appealing, accessible, bright space; possibilities to interact with other people).

Day-care centres in the experimental group also receive information resulting from the process evaluation alongside the trial. This will make it possible for them to optimize the manner in which they offer exergaming while the trial is still running. Additionally, they are offered a free training for their staff as well as specific instructions for their exergaming equipment. Day-care centres are advised to offer the exergaming intervention five times per week as a regular activity in their program. This is consistent with recommendations for physical activity for community-dwelling older people as well as those in residential care [51–54]. Research participants with dementia are encouraged to take part in the exergaming activity at least twice per week for the duration of the trial. Of course, they can participate in any other physical exercise or activities in addition the exergaming activity if they wish to do so.

### Control group: Regular activities

Participants with dementia in the day-care centres in the control group can join the regular activities. This can be a variety of recreational activities, as well as physical exercise activities such as gymnastics in a group setting, walking outdoors, etc. Day-care centres in the control group are also entitled to the same discount on the exergaming equipment and the list of optional funding organizations. However, they will not use the exergaming equipment yet for the duration of the trial.

### Outcome measures

#### Primary outcome measures

The primary outcome measures are the physical activity and mobility of the participants with dementia and can be found in Table 1. Physical activities (including exergaming) he/she is engaging in (how many times a week, and for how long) in the day-care centre and at home will be registered using a custom-developed registration form during 1 week at the three measuring moments. With regard to mobility, information will be gathered with a short physical test, the Short Physical Performances Battery (SPPB) [55]. This test consists of three subtests: balance, gait speed, and chair stand and is used to evaluate lower extremity functioning in older adults.

**Table 1 Tab1:** Primary outcome measures for participants living with dementia

Outcome	Outcome measures for participants with dementia	Recorded by	Timing		
			Baseline	3 months	6 months
Mobility	Short Physical Performance Battery (SPPB) [55]	Researcher by means of test with participant with dementia	X	X	X
Physical activities of the participant living with dementia	Custom-developed registration form	Informal caregiver	X	X	X
Physical activities of the participant living with dementia	Custom-developed registration form	Staff at day-care centre	X	X	X

#### Secondary outcome measures

##### Economic evaluation

The economic evaluation will be performed from a societal perspective. Healthcare utilization and informal care will be measured using cost diaries, and costs will be calculated according to the Dutch guidelines for economic evaluations [56]. Costs of the exergaming intervention are calculated using a bottom-up approach based on information with interviews with staff members at the day-care centre using the form ‘Costs and benefits of applied games’ [35]. Quality of life will be measured using the three-level version of the EuroQol questionnaire (EQ-5D-5 L) [57]. EQ-5D-5 L health states will be converted to utility scores using the Dutch EQ-5D-5 L tariff [58]. The utility scores will be used to calculate Quality-Adjusted Life-Years (QALYs) using the area-under-the-curve method. The secondary outcomes can be found in Tables 2, 3, and 4.

**Table 2 Tab2:** Secondary outcome measures for participants living with dementia

Outcome	Outcome measure	Recorded by	Timing		
			Baseline	3 months	6 months
Physical functioning	Physical Activity Scale of the Elderly (PASE) [67]	Researcher during interview	X	X	X
Cognitive functioning	Mini-Mental State Examination (MMSE) [68, 69]	Researcher by means of test	X	X	X
Cognitive functioning	Trail Making Test (TMT) [70]	Researcher by means of test	X	X	X
Social functioning	One question from the Adult Social Care Outcomes Toolkit (ASCOT) [71]	Researcher during interview	X	X	X
- Demographics and personal characteristics - Physical functioning - Cognitive functioning - Social functioning - Emotional functioning - Quality of life	The Older Persons and Informal Caregivers Survey Minimum DataSet (TOPICS-MDS care recipient) [72], including EuroQol five dimensions questionnaire with five-level scale (EQ-5D-5 L) [73, 74]	Researcher during interview	X	X	X
Interest in and enjoyment of physical exercise	Intrinsic Motivation Inventory (IMI) [66]	Researcher during interview	X	X	X
Satisfaction with the exergaming activity (*only experimental group*)	Separate questions	Researcher during interview	X	X	X
Body Mass Index (BMI)	Weight scale and measuring tape to measure height	Researcher during interview	X

**Table 3 Tab3:** Secondary outcome measures for informal caregivers

Outcome	Outcome measure	Recorded by	Timing			
			Baseline	3 months	6 months	0–6 months (ongoing)
Physical functioning of the participant living with dementia	Physical Activity Scale of the Elderly (PASE) [67]	Researcher during interview	X	X	X	
Fall incident rate of the participant with dementia during the past 3 months	Custom-developed registration form	Informal caregiver	X	X	X	
- Behaviour and mood of the participant living with dementia - Emotional burden for the informal caregiver	Neuropsychiatric Inventory-Questionnaire (NPI-Q) [75, 76]	Researcher during interview	X	X	X	
For both informal caregiver and participant with dementia: - Demographics and personal characteristics - Physical functioning - Cognitive functioning - Social functioning - Emotional functioning - Quality of life - Healthcare costs Experiences of the informal caregiver	The Older Persons and Informal Caregivers Survey Minimum DataSet (TOPICS-MDS informal caregiver) including EuroQol five dimensions questionnaire with five-level scale (EQ-5D-5 L) [72–74]	Researcher during interview	X	X	X	
Subjective burden for the informal caregiver	Short Sense of Competence Questionnaire (SSCQ) [77]	Researcher during interview	X	X	X	
Positive care experiences of the informal caregiver	Scale of Positive Experiences (Positieve Ervaringen Schaal (PES)) [78]	Researcher during interview	X	X	X	
- Healthcare costs - Unexpected (Adverse) Events, falls and reasons of (potential) drop out	(Care) diaries (one for the participant living with dementia, one for the informal caregiver)	Informal caregiver				X
Experience of the participant living with dementia with sports/cycling, technology and digital games in the past	Separate questions	Researcher during interview	X

**Table 4 Tab4:** Secondary outcome measures for staff at day-care centres

Outcome	Outcome measure	Recorded by	Timing		
			Baseline	3 months	6 months
- Fall incident rate of the participant with dementia during the past 3 months - Social context and extent of supervision during the exergaming activity (*only* experimental group)	Custom-developed registration form	Staff at day care centre	X	X	X
Social functioning of the participant living with dementia in the day care centre	GIP: Behaviour Observation Scale for Intramural Psychogeriatrics: sub scale 1 (Gedragsobservatieschaal voor de Intramurale Psychogeriatrie (GIP): subschaal 1) [79]	Staff at day care centre	X	X	X
Cost effectiveness	Fill out form ‘Costs and benefits of applied games’ (Invulformulier ‘Kosten en opbrengsten van applied games’) [35]	Researcher during interview (with staff of day care centre, *only experimental group*)			X
Implementation aspects of exergaming (*only experimental group*)	Measurement Instrument for Determinants of Innovations (MIDI) (MIDI: Meetinstrument Determinanten van Innovaties) [59, 60]	Online survey for staff of day care centre	X		X

